### Statistical plan

Feasibility outcomes (screening, eligibility, recruitment, retention at 12 and 24 weeks, and intervention adherence) will be analysed descriptively and presented as counts and percentages with 95% confidence intervals where appropriate.

Baseline characteristics will be summarised by randomised group using appropriate descriptive statistics (mean and standard deviation for normally distributed variables; median and interquartile range for non-normally distributed variables; frequency and percentage for categorical variables). As this is a feasibility study, no formal statistical tests of baseline differences will be conducted.

For BP outcomes (office and ambulatory measures), the number of observed participants at each time point (baseline, 12 weeks, and 24 weeks) will be clearly reported in all outcome tables. In addition, patterns of missing outcome data will be summarised descriptively by group and time point to assess the feasibility of data collection and potential differential attrition. Missingness will be explored using simple descriptive summaries (e.g., counts and percentages by group and visit) to inform planning of a future definitive trial.

Changes in BP over time between intervention and control groups will be explored using linear mixed-effects models, accounting for repeated measures within participants. The primary exploratory model will include fixed effects for group (intervention vs control), time (baseline, 12 weeks, 24 weeks), and the group × time interaction, with a random intercept for participant to account for within-subject correlation.

Given the feasibility nature of the study and sample size (n = 70), modelling will follow a parsimonious approach. The primary model will not routinely adjust for additional covariates. Covariates (e.g., socioeconomic status, medication status, physical activity) will only be included if there is strong justification, such as a clear baseline imbalance or compelling theoretical rationale. Any adjusted analyses will be considered secondary and exploratory.

Model assumptions (e.g., normality of residuals, homoscedasticity) will be assessed graphically. If substantial deviations are detected, appropriate transformations or sensitivity analyses will be considered.

All BP analyses are exploratory and intended to estimate effect sizes with 95% confidence intervals to inform the design and sample size calculation of a future fully powered randomised controlled trial. No formal hypothesis testing for efficacy is planned, and results will be interpreted cautiously in line with feasibility study objectives.

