### Outcome measurements

#### Primary outcomes.

**Feasibility outcomes:** Screening, eligibility, recruitment, and retention rates at 12 and 24 weeks.

**Exercise adherence**: Measured as the proportion of prescribed wall-squat sessions completed (from participant logs and device data), as well as mean hold time, squat stage progression, and session frequency.

**Lifestyle adherence:** Assessed by a self-reported questionnaire at 12 and 24 weeks.

**Patient Acceptability:** Determined at 24 weeks through remote, semi-structured 1:1 interviews guided by Sekhon et al.’s Theoretical Framework of Acceptability [27] and the NIH Behavior Change Consortium’s Best Practices and Recommendations [28]. Interviews will continue until data saturation is reached, which is expected to occur with 13–16 participants. Topics covered will explore experience with study participation (informed consent process, time commitment), the acceptability of measures (readability, burden), and experiences, thoughts, and attitudes toward current usual care. All interviews will be audio recorded and transcribed, and these data will be analysed thematically to generate themes and outcomes.

**Focus group discussions:** Clinical exercise physiologists and healthcare clinical professionals will be invited to participate in focus group discussions at regular intervals (~6 months) during the delivery and referral pathway. We will also characterise the remote exercise and behaviour change advice by mapping health behaviour change techniques using the 93-item BCT taxonomy (BCTTv1) [29]. This step will be crucial in informing future work to optimise the intervention and improve the transparency of the intervention content, as well as identify the targeted theoretical mechanisms of action.

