### Study power

The study will recruit a target sample of n = 70 (intervention n = 35; control n = 35) to estimate feasibility parameters (recruitment, adherence, retention, data completeness, safety) with useful precision and to provide exploratory BP effect sizes (with 95% CIs). As this is a feasibility trial, the study is not powered to test efficacy but to estimate key parameters with acceptable precision. With n = 70, the expected precision is: Retention (assume 75%): Standard error (SE) = √ [0.75 × 0.25 / 70] ≈ 0.052; 95% CI = 75% ± 10% → 65%–85%. Adherence (assume 70%): SE = √ [0.70 × 0.30 / 70] ≈ 0.055; 95% CI = 70% ± 11% → 59%–81% These confidence intervals show that with 70 participants, we can estimate retention and adherence with a margin of error of ~±10%. This is consistent with feasibility study methodology and will provide robust data to inform the design and sample size calculation for a future definitive RCT. Progression to a definitive trial will be guided by predefined traffic light criteria.

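### Exercise adherence is a fraction of sessions defined only for the 35 intervention participants, but its precision is planned as one yes/no result per person over all 70, so the printed ±11 points is not supported

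*Protocol article*

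**What the plan says.** Three sections of the protocol article bear on this.

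- **Primary outcomes.** Exercise adherence is "Measured as the proportion of prescribed wall-squat sessions completed", taken from logs and device data. The Primary aim likewise speaks of the number of sessions attended and completed. Neither place gives a cut-off that would class a participant as adherent or not.
- **Study power.** The sample is a "target sample of n = 70 (intervention n = 35; control n = 35". The planned precision is "Adherence (assume 70%): SE = √ [0.70 × 0.30 / 70] ≈ 0.055", and then "95% CI = 70% ± 11% → 59%–81"%. The section concludes that 70 participants allow retention and adherence to be estimated to within roughly ±10%.
- **Statistical plan.** Adherence stands at the end of the list of feasibility outcomes ("retention at 12 and 24 weeks, and intervention adherence) will be analysed descriptively"), all to be "presented as counts and percentages with 95% confidence intervals where appropriate".

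On who has sessions: Randomisation and Control group give the control arm the lifestyle advice and the smartwatch only. The intervention arm has three supervised sessions a week for 12 weeks and is then encouraged to continue at the same frequency.

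**The concern.** The outcome, the planning formula and the reporting form describe different quantities.

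- **Outcome:** a fraction between 0 and 1 for each intervention participant. The precision of its mean depends on how much participants differ from one another.
- **Planning formula:** √[p(1 − p)/n] is the standard error for one yes/no result per person. It suits retention. It does not suit adherence unless a threshold is defined.
- **Denominator:** 70 counts 35 control participants who have no sessions to complete.
- **Reporting form:** a count and percentage suits the per-person outcomes in the same list. For adherence the article does not say what is counted.

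Adherence is a primary outcome, and Study power offers these estimates as the basis for planning the definitive trial. A reader would take ±11 points as what the trial will deliver.

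**Working it through.** **Inputs from the article:** p = 0.70; n = 70 in the planning formula; 35 participants in the intervention arm; 3 sessions × 12 weeks = 36 Phase 1 sessions each. **Assumed, because the article gives no value:** the between-participant SD of the fraction completed, taken as 0.20, 0.30 and 0.40.

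**1. Reproduce the plan's figure.** SE = √(0.70 × 0.30 / 70) = 0.0548. Half-width = 1.96 × 0.0548 = 0.107, giving 59.3% to 80.7%. This agrees with the printed ±11 points and 59% to 81%. The arithmetic is right for the inputs used.

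**2. Same formula, with only the people who have sessions.** SE = √(0.70 × 0.30 / 35) = 0.0775. Half-width = 1.96 × 0.0775 = 0.152, giving 54.8% to 85.2%. This is √2 = 1.41 times the planned half-width.

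**3. The outcome as defined: mean of per-participant fractions, n = 35.** Half-width = 1.96 × SD/√35.

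| Assumed SD | SE | Half-width (points) | Relative to planned ±10.7 |
|---|---|---|---|
| 0.20 | 0.0338 | ±6.6 | 0.62 |
| 0.30 | 0.0507 | ±9.9 | 0.93 |
| 0.40 | 0.0676 | ±13.3 | 1.23 |
| 0.458 (maximum) | 0.0774 | ±15.2 | 1.41 |

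The maximum is √(0.70 × 0.30) = 0.458, reached when every participant completes all sessions or none. Using t(34) = 2.03 in place of 1.96 widens each interval by about 4%; at SD 0.30, ±9.9 becomes ±10.3.

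**4. When would the printed figure be right?** Setting SD/√35 equal to √(0.70 × 0.30 / 70) gives SD = √0.105 = 0.324. Below that the plan is pessimistic, and above it optimistic. Nothing in the article says where the SD will lie.

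**5. Caution on sessions as the unit (not stated in the article).** 35 × 36 = 1,260 sessions. Treated as independent, they give 1.96 × √(0.70 × 0.30 / 1,260) = 0.025, or ±2.5 points. A participant-level interval would be 2.6 times as wide at SD 0.20, 3.9 times at 0.30 and 6.0 times at the maximum; at SD 0.15 the factor is about 2.0.

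**The case against.** **The printed figure may be about right.** Assumed SDs of 0.30 and 0.35 on 35 people give ±9.9 and ±11.6 points, either side of the printed value. At equal n the yes/no formula is also the upper bound for a mean of fractions, so its form errs on the safe side. Both points stand. But the agreement comes from two departures that partly cancel: a formula that is too wide for the outcome and a denominator twice too large. It holds only near an SD that the article never states.

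**The analysis unit and interval method belong in the SAP.** That is fair for the choice between a t and a bootstrap interval, and the words 'where appropriate' leave room. It does not cover the printed precision, which is a stated figure on a denominator that cannot apply to this outcome.

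**A participant-level threshold may exist in the progression criteria, which are not shown.** If so, counts and percentages would be coherent, but the denominator would still be 35, and ±15 points would be the figure.

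**Adherence in Study power might mean lifestyle adherence, which both arms could report.** The Primary aim ties adherence to sessions, and lifestyle adherence is a separate questionnaire outcome, so this reading is strained.

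**A stronger reading.** A reader might infer that adherence intervals will be about four times too narrow because repeated sessions will be pooled. The article does not support this. It nowhere plans to pool sessions, and Study power works in participants. The factor also rests on an assumed SD, and it cannot arise from the yes/no formula. Nor would pooling distort the Phase 1 percentage: everyone is prescribed 36 sessions, so the pooled percentage equals the mean of the participants' percentages.

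**Conclusion.** The concern holds in a limited form. The stated precision for adherence uses a yes/no formula for an outcome that is a fraction, and a denominator of 70 for an outcome that exists in 35 people. On the plan's own formula the half-width should be about ±15 points (55% to 85%), not ±11; this rests only on p = 0.70 and the planned arm size. For the outcome as defined, it is about ±7 to ±13 points over assumed SDs of 0.20 to 0.40, and at most ±15. So ±11 could prove too narrow or too wide, and the design is not shown to deliver it.

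The session-pooled interval of ±2.5 points, about 2 to 6 times too narrow, is a caution about one way the reporting sentence could be carried out. It does not describe what is planned. The retention precision is unaffected: all 70 participants contribute one yes/no result each, and √(0.75 × 0.25 / 70) = 0.052 gives ±10 points as printed.

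**What to change.** **Statistical plan.** Take adherence out of the shared sentence. State that each intervention participant's fraction of prescribed sessions completed will be computed and summarised as mean (SD) or median (IQR), with a 95% interval that takes the participant as the unit (t or bootstrap, n = 35). If progression uses a yes/no threshold, state it and report the number of participants meeting it out of 35.

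**Study power.** Restate the adherence precision on n = 35 for whichever measure is chosen: about ±15 points for a threshold at 70%, or a range over stated SD assumptions for a mean fraction. Limit the claim of about ±10% with 70 participants to retention.

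**Cost.** One or two sentences and one recalculated figure. No change to the sample size, data collection or conduct of the trial is needed.

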### Randomisation

Individuals who meet the study criteria and agree to participate will be randomly assigned to one of two parallel groups: (1) remotely supervised leg IET and behaviour change advice, or (2) a control group behaviour change advice and smartwatch only. Randomisation will be performed with minimisation for sex and the mean of office systolic BP (≤140 mm Hg vs > 140 mm Hg).

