#### Secondary outcomes.

This study will assess the feasibility and acceptability of collecting BP data, considering the perspectives of participants and healthcare clinical professionals (Healthworks team), as well as data collection challenges and missing data rates. Findings will inform the suitability of these measures for a future full-scale trial. Assessments will be conducted at baseline (pre-randomisation), 12 weeks, and 24 weeks at Northumbria University, Newcastle upon Tyne, UK. Office BP will be measured using an Omron HEM-742 device. Participants will sit quietly for five minutes, and readings will be taken at one-minute intervals on the right arm until a difference of less than 4 mmHg is achieved between two consecutive measurements. The average measurements will be calculated to determine the office systolic and diastolic BP. Ambulatory BP will be measured using a non-invasive oscillometric device (Welch Allyn ABPM 7100 Central Blood Pressure, USA) worn on the nondominant arm, recording measurements every 15 minutes over 24 hours. Mean systolic, diastolic, and overall BP will be calculated for the full 24-hour period, as well as during awake and asleep periods. BP variability will be assessed using 24-hour standard deviation, weighted SD (SDdn), and average real variability (ARV24).

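### The BP model ignores that baseline precedes randomisation: its change contrast is unbiased, but its 95% CI is about 5–15% wider than a baseline-adjusted one and can be miscalibrated

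*Protocol article*

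**What the plan says.** The Statistical plan of the protocol article states the target: "Changes in BP over time between intervention and control groups will be explored using linear mixed-effects models". The primary exploratory model has "fixed effects for group (intervention vs control), time (baseline, 12 weeks, 24 weeks), and the group × time interaction". Baseline is thus one of three outcome visits, and the model has 2 × 3 = 6 free cell means, two of them at baseline. Repeated measures on one person are handled by a single term: "with a random intercept for participant to account for within-subject correlation".

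On adjustment, the same section says: "The primary model will not routinely adjust for additional covariates". Covariates enter only with strong justification, "such as a clear baseline imbalance or compelling theoretical rationale", and such analyses are secondary. Baseline BP is not a covariate, and the minimisation factors are not named.

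Two design facts bear on this. Under Secondary outcomes: "Assessments will be conducted at baseline (pre-randomisation), 12 weeks, and 24 weeks". Under Randomisation: "Randomisation will be performed with minimisation for sex and the mean of office systolic BP", cut at 140 mmHg.

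The end of the Statistical plan says that the BP analyses are exploratory, that no efficacy test is planned, and that the effect sizes and 95% CIs are meant to inform the design and sample size of the definitive trial.

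**The concern.** Because baseline BP is taken before allocation, the expected baseline means of the two arms are equal by design. The planned model still estimates a baseline difference and removes all of it through the interaction. That is a comparison of mean changes. Regression on baseline removes only the fraction ρ of the chance imbalance, which is the more precise choice for any ρ below 1.

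A random intercept as the only covariance term also imposes one variance and one correlation on all three pairs of visits. If 12 and 24 weeks correlate more strongly with each other than with baseline, or if correlation decays with time, the standard error of a change from baseline is wrong. The assumption checks that the article names as examples (residual normality, homoscedasticity) do not examine this.

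At stake are the width and the calibration of the intervals that are to be carried forward to the definitive trial.

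**Working it through.** **Inputs from the article.** 70 participants, 35 per arm, and 75% retention (Study power), so 0.75 × 35 ≈ 26 per arm; model, timing of baseline and minimisation factors as quoted.

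**Inputs assumed.** The article gives no BP standard deviation (SD) and no correlation. I take SD 15 mmHg and ρ from 0.3 to 0.8.

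**The plan's own figures.** The only precision stated is for retention and adherence. It reproduces: sqrt(0.75 × 0.25/70) = 0.0518, ±10.1 points; sqrt(0.70 × 0.30/70) = 0.0548, ±10.7 points. There is no BP figure to reproduce.

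**Step 1: width.** With complete data and a common variance σ², n per arm:
- planned contrast: variance 2σ²(1−ρ) × 2/n
- baseline-adjusted contrast: variance σ²(1−ρ²) × 2/n
- variance ratio 2/(1+ρ); CI-width ratio sqrt(2/(1+ρ))

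Half-width = t(0.975; 50 df) × 15 × k × sqrt(2/26), with t = 2.009 and k = sqrt(2(1−ρ)) or sqrt(1−ρ²):

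| ρ | Width ratio | Planned (mmHg) | Adjusted (mmHg) |
|---|---|---|---|
| 0.3 | 1.24 | 9.9 | 8.0 |
| 0.5 | 1.15 | 8.4 | 7.2 |
| 0.7 | 1.08 | 6.5 | 6.0 |
| 0.8 | 1.05 | 5.3 | 5.0 |

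With missing visits the identity is approximate.

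**Step 2: what minimisation recovers for office systolic BP.** Let f be the share of baseline-imbalance variance that the allocation removes. The planned contrast then has true variance proportional to (1−ρ²) + (1−ρ)²(1−f), so the ratio to the adjusted contrast is 1 + (1−f)(1−ρ)/(1+ρ). With f = 0 this is 2/(1+ρ). Perfect balance on a normal baseline cut at its mean gives f = 2/π = 0.64; losing 25% at random leaves f ≈ 0.75 × 0.64 = 0.48. The ratio is then 1 + 0.52 × 0.333 = 1.17 at ρ 0.5 and 1 + 0.52 × 0.176 = 1.09 at ρ 0.7.

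Simulation (6,000 trials per setting; 70 participants; minimisation on sex and systolic BP at 140 mmHg with assumed allocation probability 0.9; mean systolic BP 135 or 140; 75% retained at random) agrees: about 1.16–1.18 at ρ 0.5 and 1.07–1.10 at ρ 0.7, against 1.33 and 1.18 from 2/(1+ρ). About half of the true loss is recovered. The planned standard error does not reflect this: with equal correlations of 0.6 and arms balanced on dichotomised baseline, simulated coverage is about 96%.

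**Step 3: calibration when correlations differ.** The random-intercept model takes the variance of a change as 2σ²(1−mean ρ); the true value at visit t is 2σ²(1−ρ between baseline and t). Correlations below are baseline–12, baseline–24 and 12–24 weeks.
- 0.6, 0.5, 0.7: at 24 weeks the model uses 0.8σ² and the truth is 1.0σ². Coverage = 2Φ(1.96 × sqrt(0.8)) − 1 = 92.0%.
- 0.7, 0.5, 0.7: the model uses 0.733σ²; the truth is 0.6σ² and 1.0σ². Coverage is 97.0% at 12 weeks and 90.7% at 24 weeks.
- 0.5, 0.4, 0.7: 94.2% and 91.6%.
- 0.6, 0.6, 0.8: 92.6% at both visits.
- Equal correlations: 95.0%.

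With arms balanced on dichotomised baseline, simulated coverage moves up: 97.7% and 93.2% for the second pattern, 96.0% and 94.7% for the third, 94.2% at both visits for the fourth. Baseline-adjusted analysis at each visit stayed at 94.5–95.6% in these simulations.

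**The case against.** The planned model is conventional and valid, and the article defends it by parsimony at n = 70. BP is a secondary outcome, unpowered and untested, and progression rests on traffic-light criteria. A half-width of 7.2 rather than 8.4 mmHg is still imprecise, and no design decision has been shown to turn on it. Every number rests on an assumed SD and ρ; ambulatory means, averaged over many readings, may have a high ρ and so a small gain. Degrees of freedom and covariance detail are often left to an analysis plan that is not shown. The article also does not name the interaction coefficient as the reported estimate.

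Much of this stands, and it lowers the severity. It does not remove the point. The article itself fixes the fixed effects and the random intercept. Parsimony does not favour free baseline means: a common baseline uses five mean parameters instead of six. If a raw group difference at a visit were reported instead, it too would be unadjusted for baseline.

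Four stronger readings are tempting and are not supported:
- **The estimate is biased.** It is not; randomisation protects it.
- **The plan wastes the equivalent of 18–33% more participants.** That takes 2/(1+ρ) at ρ 0.7 and 0.5 and ignores minimisation; for office systolic BP the true loss is about half of that. The full formula is closer for outcomes that minimisation does not balance.
- **The effect estimates are all that the BP analysis yields.** The secondary aim is the feasibility of collecting BP data, and observed counts and missingness are also planned.
- **The interval is both too wide and too narrow.** Over-coverage and under-coverage arise under different correlation patterns, or at different visits within one pattern.

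**Conclusion.** The point holds, at low to moderate severity. The planned contrast is unbiased, but its model-based 95% CI is wider than the baseline-adjusted one by about 15% at ρ 0.5, 8% at ρ 0.7 and 5% at ρ 0.8. For office systolic BP the excess in true sampling variance is smaller, a ratio of about 1.17 at ρ 0.5 and 1.07–1.10 at ρ 0.7, so the interval is conservative if correlations are equal. If they are not, it can be too narrow at one visit: about 91–94% coverage under the unequal patterns tried, with over-coverage at the other visit in some of them.

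The width ratio depends only on ρ and equal variances. The mmHg figures also assume SD 15 and 26 per arm, and the minimisation figures assume a near-normal baseline and loss at random.

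**What to change.** Replace the model description with one of these:
1. A constrained longitudinal model: one baseline mean common to both arms, with group effects only at 12 and 24 weeks.
2. A repeated-measures model of 12- and 24-week BP, with baseline BP and baseline-by-visit as covariates.

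In either case include the minimisation factors; in the second, baseline BP in continuous form already carries the office systolic factor when that is the outcome. Use an unstructured covariance (3 × 3 in the first model, six parameters) with a small-sample correction such as Kenward–Roger, and name a simpler structure as the fallback if the model does not converge. Report the adjusted mean difference and 95% CI at each visit.

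The cost is about two sentences and no new data. The downside is a few more covariance parameters to estimate from 70 participants.

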### Inclusion criteria

Diagnosis of AH in accordance with NICE guidelines.Under pharmacological treatment for AH with antihypertensive drug, type and dose maintained for the previous four months.Blood Pressure with values <180 and <110 mmHg for office systolic and diastolic BP, respectively.Not currently engaged in any structured or supervised exercise training programme, including resistance, aerobic, or isometric exercise, defined as planned exercise performed ≥2 times per week at moderate or greater intensity, for at least three months prior to enrolment.

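### The primary BP model uses baseline BP only as an unconstrained response and leaves out the minimisation factors, which costs precision but causes no bias; the rule for secondary covariates also needs tightening

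*Protocol article*

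**What the plan says.** The Randomisation section states: "Randomisation will be performed with minimisation for sex and the mean of office systolic BP", with the systolic value split at 140 mmHg. Both factors are therefore known for every participant before allocation.

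The Statistical plan fixes the primary exploratory BP model as "fixed effects for group (intervention vs control), time (baseline, 12 weeks, 24 weeks), and the group × time interaction". Repeated measures are handled by a single random effect, a participant-level intercept. On adjustment it says: "The primary model will not routinely adjust for additional covariates". Neither sex nor office systolic BP category is named as a model term anywhere in that section.

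On other covariates it says: "Covariates (e.g., socioeconomic status, medication status, physical activity) will only be included if there is strong justification, such as a clear baseline imbalance". A theoretical rationale is a second permitted reason. Analyses adjusted in this way are labelled secondary and exploratory. The section does not say when the example covariates are to be measured.

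The same section plans no efficacy test and says that the BP estimates and their 95% CIs are to help design and size the definitive trial.

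**The concern.** Two things look wrong.

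First, the design uses sex and baseline systolic BP to allocate, but the model does not use them to estimate. When allocation is balanced on a variable that predicts outcome, an analysis that ignores it reports a standard error larger than the estimate's true variability. Baseline BP is also the strongest predictor of later BP that the trial is likely to have, and the stated model does not use it efficiently. The BP intervals are an intended product of this pilot, so avoidable width carries into planning the next trial.

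Second, the rule for admitting covariates into secondary analyses depends on what the data show. It has no threshold, and formal baseline tests are ruled out, so the decision rests on judgement after seeing the table. Two of the three examples, medication status and physical activity, can change after randomisation, and nothing in the text ties them to baseline values.

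**Working it through.** **The plan's own figures.** The only numerical justification is for feasibility (Study power), and it reproduces:
- Retention: √(0.75 × 0.25 / 70) = 0.0518; 1.96 × 0.0518 = 0.101; CI 64.9% to 85.1%.
- Adherence: √(0.70 × 0.30 / 70) = 0.0548; 1.96 × 0.0548 = 0.107; CI 59.3% to 80.7%.

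No SD, correlation or effect size is given for BP, so what follows rests on assumptions.

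**Inputs.** From the article: 35 per arm, 75% retention, visits at baseline, 12 and 24 weeks. Assumed: SD σ = 15 mmHg; within-person correlation ρ = 0.5 or 0.7; a sex difference of 5 or 6 mmHg; minimisation favouring the balancing arm with probability 0.8.

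**Closed form, complete data.** With all visits observed, the stated group × time estimate at 24 weeks is the difference between arms in mean change from baseline.
- Stated model: SE = √[2σ²(1 − ρ) × 2/35]. For ρ = 0.5: √(225 × 2/35) = 3.59 mmHg. For ρ = 0.7: √(135 × 2/35) = 2.78.
- Baseline as covariate: SE = √[σ²(1 − ρ²) × 2/35]. For ρ = 0.5: √(168.75 × 2/35) = 3.11. For ρ = 0.7: √(114.75 × 2/35) = 2.56.
- Ratio: √[(1 + ρ)/2] = 0.866 and 0.922, so the variance falls by 25% and 15%.

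**Simulation** (150 trials per row, minimisation as planned, no true effect). Mean model SE of the 24-week contrast, in mmHg:

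| Data, ρ | Stated model | + sex and SBP category, main effects | + both factors × time | Constrained baseline + sex | 24-week ANCOVA + sex |
|---|---|---|---|---|---|
| Complete, 0.5 | 3.56 | 3.56 | 3.38 | 3.08 | 3.09 |
| Complete, 0.7 | 2.76 | 2.76 | 2.68 | 2.54 | 2.54 |
| 25% dropout, 0.5 | 4.00 | 3.92 | 3.72 | 3.55 | 3.60 |
| 25% dropout, 0.7 | 3.12 | 3.08 | 2.99 | 2.92 | 2.98 |

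The constrained-baseline model cuts the SE by 1 − 3.08/3.56 = 13%, 1 − 2.54/2.76 = 8%, 1 − 3.55/4.00 = 11% and 1 − 2.92/3.12 = 6%. ANCOVA on completers gives similar cuts, except in the last row (1 − 2.98/3.12 = 4%). In the first row the CI half-width goes from 1.96 × 3.56 = 7.0 mmHg to 1.96 × 3.08 = 6.0 mmHg.

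**Where the gain comes from.** With complete data, adding the two factors as main effects left the estimate identical in every run, because anything constant within a person cancels from a change. With dropout the SE moved by only 1 to 2%. A further simulation (3,000 trials, 75% retained, ρ = 0.5) separated the parts:
- change score 4.15; change score plus sex 4.16
- ANCOVA on baseline 3.62; ANCOVA plus sex 3.61

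Sex contributes almost nothing to precision. At ρ = 0.7 the corresponding change-score and ANCOVA values were 3.21 and 2.99.

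**Calibration.** The stated model's mean SE exceeded the empirical SD by 6 to 13% (for example 3.56 against 3.35, and 4.00 against 3.53). Coverage was 0.947 to 0.973, known only to about 3 to 4 points with 150 runs. A run of 6,000 trials, at ρ = 0.5 and 75% retained, gave SE 4.16 against SD 3.96 and coverage 96.1%. The error is on the conservative side.

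**Covariates.** Entry requires: "Under pharmacological treatment for AH with antihypertensive drug, type and dose maintained for the previous four months". On/off treatment therefore cannot differ at baseline, although drug class or number can. The physical-activity measurements described in the text come after allocation: the watch is supplied to allocated participants, and the lifestyle questionnaire is at 12 and 24 weeks. The schedule figure is not shown and may list a baseline measure.

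**The case against.** The best defence is that the primary model is prespecified, simple and suited to a feasibility trial of 70. Baseline office systolic BP is not ignored, since it is the first response in the model. No efficacy test is planned, the interval errs on the safe side, and anything adjusted is secondary. All of this stands, and it limits the priority of the point. It does not remove the loss of precision in estimates that are meant to inform the next trial.

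Four stronger readings are tempting, and the documents do not support them.

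- A reader might infer that the primary CI is invalid because the minimisation factors are missing. The calculations show slight over-coverage, with no bias and no under-coverage.
- A reader might credit the gain to the minimisation factors as such. It comes from using baseline BP efficiently, and it would be available under simple randomisation too.
- A reader might infer that the primary result depends on which imbalances appear. It does not: imbalance-triggered models are secondary and leave the primary model unchanged.
- A reader might infer that the plan will adjust for post-randomisation medication or activity. It does not say so, and the reference to baseline imbalance points towards baseline values. The theoretical-rationale route carries no such limit, so the wording permits on-study values without planning for them.

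**Conclusion.** The point holds as one of efficiency and wording. The primary BP model omits both minimisation factors as covariates and treats baseline BP as an unconstrained response. Under the assumed SD of 15 mmHg and correlations of 0.5 to 0.7, baseline adjustment would reduce the 24-week SE by about 6 to 14%, nearly all of it through baseline BP. The gain shrinks as the correlation rises. The percentages do not depend on the SD in the closed form, but the mmHg values do. For diastolic and ambulatory outcomes, office systolic BP is absent from the model altogether; the size of that effect was not calculated.

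The secondary-analysis rule is data-driven and leaves the timing of covariates open. Priority is low to moderate, since every BP analysis is exploratory and the primary outcomes concern feasibility.

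**What to change.** 1. For each BP outcome, make the primary model baseline-adjusted. Either model the 12- and 24-week values with the outcome's own continuous baseline as a covariate, or keep three visits in a mixed model with baseline means constrained equal across arms. The second option keeps participants who have no follow-up values.
2. Include sex and baseline office systolic BP (continuous). For office systolic BP, the baseline value already represents the second factor. Adding the factors as main effects to the present model is not enough, since with complete data that changes nothing.
3. For secondary adjusted analyses, remove observed imbalance as a trigger, list the covariates in advance, and require that each be measured before randomisation. Report on-study medication changes and activity by arm descriptively.

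The cost is wording. Both factors are already recorded in order to randomise. The model spends one or two degrees of freedom for office systolic BP, and at most three for other outcomes if their own baseline is a covariate, against about 52 participants expected at 75% retention (0.75 × 70 = 52.5).
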